##### The National Institutes of Health Stroke Scale

2.5.1.4

The National Institutes of Health Stroke Scale (NIHSS) is a standardized tool used to quantify stroke severity (46). It evaluates impairment in 11 domains including consciousness, eye movements, visual fields, facial palsy, limb strength, sensation, coordination, language, speech, and neglect. The total NIHSS score sums all domain scores and ranges from 0 to 42, with higher totals signifying greater stroke impact.

##### Tolerability and safety

2.5.1.5

This study will use a 16-item symptom questionnaire to rate the subjective symptom [headache, scalp pain, arm/hand pain, other pain(s), numbness/tingling, other sensation(s), weakness, loss of dexterity, vision/hearing change(s), ear ringing, nausea/vomiting, appetite loss, rash, skin change(s) or any other symptom(s)] on a scale of 0 to 5 (none, minimal, mild, moderate, marked, severe) prior to any TMS application (47). Assessments will be made at the end of each treatment session to detect the presence of any adverse events.

#### Neurophysiological examinations

2.5.2

Patients will be seated in a comfortable chair approximately 60 cm from a computer monitor in an electrically shielded room. EEG signal will be record by the NeuroScan EEG acquisition system (64-channel EEG cap, EEG amplifiers, signal converters, and CURRY 8.0 software). Stimulation presentation will be programmed in E-Prime 3.0 (Psychology Software Tools Inc., Pittsburgh, PA). The electrodes will be positioned in accordance with the international standard EEG 10–20 system, and the resistance ≤ 10 kΩ. Patients will be instructed to remain still, silent, and refrain from extraneous movements during the recording session.

##### Resting-state EEG

2.5.2.1

Patients will be directed to remain motionless, fixate their attention on the “+” symbol located in the screen’s center, stay alert and avoid sleepiness throughout the recording. A 10-min continuous EEG signal will be recorded.

##### Event-related potentials

2.5.2.2

N400: The visual stimulation used for this study comprise semantically related pairs of pictures and words. The pictures are obtained from an international picture database and consisted of 120 common object images (48). Each image is sized at 300 × 300 pixels and present in Microsoft YaHei font with a font size of 24. The pictures are displayed for a duration of 1 s. Subsequently, the target word appears at the same position as the previous picture and remain on the screen for 3 s (49). Patients are instructed to judge as quickly and accurately as possible whether the target word is consistent or inconsistent with the preceding picture by pressing the left mouse button for consistent and the right mouse button for inconsistent. The longer presentation duration of the target word was to provide sufficient time for patients to make judgments and responses. Patients’ choices and reaction times were recorded by E-Prime software. MMN: The auditory stimulation is presented binaurally through insert earphones at an intensity of 70 dB sound pressure level. The stimulation consisted of 1,000 and 1,500 Hz pure tones occurring at frequencies of 90% and 10%, respectively. Each tone is presented for 50 ms. In total, 500 stimulations are delivered in each experimental block, comprising approximately 5 min and 45 s. The frequent 1,000 Hz tones is served as standard stimulation, while the infrequent 1,500 Hz tones are deviant stimulation in this auditory oddball paradigm (50).

#### Neurochemical assessment

2.5.3

To investigate serum biomarkers related to synaptic plasticity and neuronal excitability, 5 mL blood samples will be collected from patients before and after treatment. Then those blood promptly centrifuged at 3,000 r/min for a duration of 10 min to facilitating serum separation. The resultant serum is aliquoted and preserved at −80°C for further analyses.

### Data analysis

2.6

All data will be analyzed by professional statisticians using SPSS software (Version 25.0; IBM, Armonk, NY, United States). Baseline characteristics will be described using means ± standard deviations for continuous variables and frequencies for categorical variables. Prior to applying independent sample t-tests or Mann–Whitney U tests for continuous variables, a normality test will be conducted using either the Kolmogorov–Smirnov or Shapiro–Wilk test. Categorical variables will be compared using chi-square tests or Fisher’s exact tests. The primary outcome is the change in WAB-R scores before and after treatment. The secondary outcomes include changes in blood markers, EEG, and ERP indices before and after treatment. These measures will be analyzed using a Linear Mixed Effects Model (LMM), where group acts as a fixed effect, time points as a repeated measure, and patients as random effects within the LMM framework. If significant interaction effects between groups and time points are revealed by the LMM, post-hoc comparisons will be conducted to identify the time points at which differences occur, using methods like Bonferroni-corrected pairwise comparisons.

The acquired EEG signals will be analyzed using MATLAB2021b. The EEGLAB toolbox (version 2023.0) will be used for EEG data preprocessing (51). MMN and N400 components in the ERP data will be extracted through time-window analysis and peak detection techniques. EEG data analysis will focus on power spectral analysis to assess changes in key EEG frequency bands, such as alpha and beta bands (52). These data will be analyzed within the LMM framework to examine the patterns of change before and after treatment and their correlation with clinical improvement. If the LMM reveals significant interaction effects between groups and time points, appropriate post-hoc comparisons, such as Bonferroni-corrected pairwise comparisons, will be conducted to identify the specific time points at which differences occur.

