### Study design

2.1

This is a randomized, double-blinded, sham-controlled trial. The study will adhere to the ethical principles outlined in the Declaration of Helsinki and will follow the Consolidated Standards of Reporting Trials (CONSORT) guidelines (38), as well as the Recommendations for Interventional Trials (SPIRIT) (39). All patients who meet the inclusion and exclusion criteria will be randomly assigned in a 1:1 ratio to the following piTBS group and sham group after obtaining written informed consent. All patients will undergo corresponding assessments before treatment (T0), after treatment (T1), as well as during the 4-weeks follow up (T2). Please refer to Figure 1 and Table 1 for the specific study process. This study has been approved by the Medical Ethics Committee of the China Rehabilitation Research Center (No.2023-027-2) and registered in the Chinese Clinical Trial Registry (No. ChiCTR2300074533).

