#### Inclusion criteria

2.2.1

The patients were diagnosed with ischemic or hemorrhagic stroke with the lesion located in the left hemisphere, with a disease duration ranging from 1 to 12 months;The patients will undergo assessment for aphasia using the Western Aphasia Battery Revised (WAB-R), and the WAB-R aphasia quotient will be less than 93.8 points;Patients aged 18–75 years;Right hand;Normal language function before the onset of the disease;The native language is Chinese, primary school education or above (with more than 6 years of education).

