### Randomization and blinding

2.3

The randomized sequence of numbers generated by SPSS software will be written in order and placed in opaque sealed envelopes. All eligible patients will be randomly assigned to one of the two treatment groups in the order of enrollment. Recruiters, study physicians, TMS operators, clinical staff, evaluators, data collectors and statistical analysts are blinded. These people will not know the group of patients.

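### The primary model compares raw changes, without adjusting for baseline AQ or months since stroke: this causes no bias, but it gives up precision and leaves chance imbalance unadjusted with 15 per arm

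*Protocol article*

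**What the plan says.** Section 2.6 defines the endpoint: "The primary outcome is the change in WAB-R scores before and after treatment". It gives the model as one "where group acts as a fixed effect, time points as a repeated measure, and patients as random effects within the LMM framework", and the decision step as: "If significant interaction effects between groups and time points are revealed by the LMM, post-hoc comparisons will be conducted". No baseline covariate is named.

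Section 2.2.1 admits patients "with a disease duration ranging from 1 to 12 months" and requires that "the WAB-R aphasia quotient will be less than 93.8 points", with no lower limit on AQ. Table 1 schedules the WAB-R at T0, T1 and T2, so baseline AQ is measured in everyone. Time since stroke is an eligibility item, so it too is known at entry.

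On allocation, section 2.3 says: "The randomized sequence of numbers generated by SPSS software will be written in order and placed in opaque sealed envelopes", and then "All eligible patients will be randomly assigned to one of the two treatment groups in the order of enrollment". It describes no stratification or minimisation. Section 2.2.4 sets 15 patients per arm, 28 evaluable in total.

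**The concern.** With T0 kept as an outcome and each arm free to have its own T0 mean, the T0-to-T1 part of the interaction is, with complete data, the difference between arms in mean raw change. That is a legitimate estimate, but it gives the baseline a fixed weight of one. A baseline-adjusted analysis gives it the weight that the data support, and so has a smaller variance unless the baseline and follow-up scores are very highly correlated.

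Time since stroke enters neither the allocation nor the model. Someone one month after stroke may well change more over three weeks than someone at twelve months. If so, part of the spread in change is predictable from a value already on file, and the stated model leaves it in the error term. In a trial of 30, that spread is costly, and a chance difference between arms in recovery stage could not be allowed for in the primary analysis.

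**Working it through.** **The plan's own figure.** Section 2.2.4 gives N = 28 for f(V) = 0.25, alpha 0.05, power 0.95, two groups and three times, but no correlation between measurements. I entered 0.25 as an ordinary f in the within-between interaction test: λ = f²·N·m/(1−r), with 2 and 52 degrees of freedom at N = 28.

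- r = 0.5: λ = 0.0625 × 28 × 3 / 0.5 = 10.5. Power is 0.81, and 44 patients would be needed for 0.95.
- r = 0.70: λ = 5.25 / 0.30 = 17.5. Power is 0.96.

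So 28 comes back only at an unstated r of about 0.68 to 0.70. That is a separate issue. It matters here only as a hint of the r the plan may have had in mind.

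**Baseline AQ.** Take equal variances at T0 and T1, scaled to 1.

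- Raw change: variance 2(1−r).
- Baseline-adjusted: variance 1−r².
- Ratio: (1−r²)/(2(1−r)) = (1+r)/2.
- Cost of one estimated slope: a factor 1 + 1/(N−4), which is 25/24 = 1.042 at N = 28.

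| r (assumed) | Variance ratio | SE reduction | 30 patients act like | Ratio after df cost |
|---|---|---|---|---|
| 0.5 | 0.75 | 13.4% | 40 | 0.78 |
| 0.7 | 0.85 | 7.8% | 35 | 0.89 |
| 0.8 | 0.90 | 5.1% | 33 | 0.94 |
| 0.9 | 0.95 | 2.5% | 32 | 0.99 |

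The third and fourth columns are before the degree-of-freedom cost. Break-even: (1+r)/2 × 25/24 = 1 gives r = 48/25 − 1 = 0.92.

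**Months since stroke.** If it explains a share R² of the residual variance (assumed), the net factor at N = 30 is (1−R²)(1 + 1/26).

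- R² = 0.05: 0.95 × 1.038 = 0.99
- R² = 0.10: 0.90 × 1.038 = 0.93
- R² = 0.20: 0.80 × 1.038 = 0.83

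**Both together.** The factor is (1+r)/2 × (1−R²) × (1 + 2/25). With R² = 0.20 this is 0.73 at r = 0.7 and 0.82 at r = 0.9. A simulation of 8,000 trials per setting, 15 per arm, agrees. The SD of the estimate fell from 0.282 to 0.243 at r = 0.7, and (0.243/0.282)² = 0.74. It fell from 0.165 to 0.150 at r = 0.9, and (0.150/0.165)² = 0.83.

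**Bias and type I error without adjustment.** In the same simulation, with months explaining 20% of residual variance, the raw-change analysis had bias 0.005 and 0.000 SD and type I error 0.048 and 0.055 (r = 0.7 and 0.9). The Monte Carlo standard error is √(0.05 × 0.95/8000) = 0.0024, so both rates lie within about two standard errors of 0.05.

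**Chance imbalance.** The standardised difference between arms of 15 has standard error √(2/15) = 0.365. The probability that it exceeds 0.5 in absolute size is 2(1 − Φ(0.5/0.365)) = 0.17. If months since stroke were uniform on 1 to 12 (assumed), the SD would be 11/√12 = 3.2 months and the SE of the arm difference 3.18 × 0.365 = 1.16 months. A gap of more than two months would then occur 8.5% of the time.

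**The case against.** The strongest reply is that nothing stated is wrong. A group-by-time mixed model with T0 as a repeated outcome is a standard, valid analysis of change, and a journal article may leave covariates and strata to a fuller plan. The validity stands. The second part stands only in part, because section 2.6 does set out the model's terms and decision rule. The point rests on those terms.

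A reader might infer that recovery stage confounds the treatment effect, or that spontaneous recovery is not separated from it. The documents do not support that. Allocation is random, and the sham arm receives the same speech therapy over the same three weeks, so spontaneous recovery is shared on average. What remains is chance imbalance and lost precision.

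A reader might also infer that baseline AQ is ignored. It is not: T0 is in the model and each patient's starting level is already removed. Only the step from raw change to baseline adjustment is forgone.

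Nor is adjustment always more precise. Above about r = 0.92 the lost degree of freedom outweighs the gain, and a composite score repeated about three weeks later could be that stable.

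Finally, the power gain may be small. If the effect is equal at T1 and T2, f = 0.25 implies a T1 difference of 0.25 × √18 = 1.06 SD. With 14 per arm, adjusting for AQ then lifts power from 77% to 86% at r = 0.5, but only from 94% to 96% at r = 0.7, near the value that reproduces N = 28. The time profile is also unstated, so neither pair of figures can be claimed for this trial.

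**Conclusion.** The point holds as one of efficiency and pre-specification, not of bias. The stated model has no term for time since stroke, uses baseline AQ only as the T0 outcome, and is paired with an allocation for which no balancing on either is described. Type I error is kept.

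The gain from adjusting for AQ is moderate at low r (variance factor 0.75 at r = 0.5), small at high r (0.95 at r = 0.9, or 0.99 after the degree-of-freedom cost) and gone above about 0.92. Months since stroke could bring almost nothing or a variance reduction of about 17%, depending on whether it explains 5% or 20% of residual variance. Both r and R² are assumptions, since the documents give neither. The change is still worth making, because both values are known for every patient and covariates chosen after unblinding would carry little weight in a trial of 30.

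**What to change.** In section 2.6, adopt one of two forms before unblinding.

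- **Baseline as covariate.** Model T1 and T2 AQ as outcomes, with group, time, group-by-time, baseline AQ and months since stroke. T0 is then no longer an outcome, so the interaction shows only whether the effect differs between T1 and T2. The primary test must therefore be named as the group contrast at T1.
- **Common baseline.** Keep T0 as an outcome, constrain the arms to the same T0 mean, and add months since stroke by time. A main effect of months alone would shift all three time points equally and would not adjust the change.

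Use the matching baseline value for each secondary outcome: T1 and T2 for SAQOL-39 g, and T1 only for EEG, ERP and BDNF, which Table 1 schedules at T0 and T1 only.

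The cost is a few sentences and two degrees of freedom, with no new data. In the worst case, r close to 1 and months uninformative, the variance rises by a factor of about 1.08, or √1.08 = 1.04 in the standard error. Stratified envelopes are optional and not needed for this fix.

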**Methods:**

This is a randomized, double-blinded, sham-controlled trial. A total of 30 PSA patients will be randomly allocated to receive either piTBS stimulation or sham stimulation for 15 sessions over a period of 3 weeks. The primary outcome is the Western Aphasia Battery Revised (WAB-R) changes after treatment. The secondary outcomes include The Stroke and Aphasia Quality of Life Scale (SAQOL-39 g), resting-state electroencephalogram (resting-state EEG), Event-related potentials (ERP), brain derived neurotrophic factor (BDNF). These outcome measures are assessed before treatment, after treatment, and at 4-weeks follow up. This study was registered in Chinese Clinical Trial Registry (No. ChiCTR23000203238).

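### A patient random effect over three WAB-R visits can mis-size the standard errors of the T0-T1 and T0-T2 contrasts in either direction; an unstructured covariance avoids this at little cost

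*Protocol article*

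**What the plan says.** Protocol article, 2.6 Data analysis, describes a model with a fixed group effect, "time points as a repeated measure, and patients as random effects within the LMM framework". The software is SPSS 25. The same section defines the primary outcome: "The primary outcome is the change in WAB-R scores before and after treatment". If the group-by-time interaction is significant, "post-hoc comparisons will be conducted to identify the time points at which differences occur, using methods like Bonferroni-corrected pairwise comparisons".

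Section 2.1 and Table 1 place WAB-R at T0, T1 and T2. Treatment is given "for 15 sessions over a period of 3 weeks" (abstract, Methods), and T2 is the 4-week follow-up. Section 2.2.1 admits patients "with a disease duration ranging from 1 to 12 months".

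The article names no residual covariance type and gives no WAB-R SD, between-visit correlation or spread of recovery rates.

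**The concern.** A patient intercept gives every pair of visits the same covariance. With a constant residual variance it also gives every pairwise change the same variance. That fits if all patients recover alike apart from noise. In a sample 1 to 12 months after stroke, with any aphasia quotient below 93.8, recovery is likely to differ between patients, and the three changes then have different variances. The model averages them, so some contrasts get a standard error that is too large and others one that is too small.

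The T0-T1 contrast carries the primary outcome. Too large a standard error there can hide a real gain, and too small a one can produce a false positive. At T0-T2 the same errors affect any claim of a lasting effect. With 15 patients per arm, the size of these errors matters.

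**Working it through.** The plan has no figure of its own on this point, so there is nothing to reproduce. All SDs below are assumptions.

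**Inputs.** From the article: 15 per arm, three visits, 3 weeks of treatment. Reading T2 as 4 weeks after T1 puts the visits at weeks 0, 3 and 7. Assumed: complete data, a stable between-patient SD that cancels from changes, visit-level error SD e, and individual recovery on top.

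**1. Worked example: patients diverge linearly, rate SD s per week.** The change variances are:
- T0-T1: 9s² + 2e²
- T1-T2: 16s² + 2e²
- T0-T2: 49s² + 2e²

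With s = 1 and e = 2 these are 17, 24 and 57. A constant-residual patient intercept uses their mean, 98/3 = 32.7, for all three. Model SE / true SE is √(32.7/17) = 1.39 for T0-T1 and √(32.7/57) = 0.76 for T0-T2.

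**2. Other shapes of recovery.** Let the largest individual-recovery SD over the visits be k residual SDs. In units of e², with k = 2:
- Linear: variances 2.73 (T0-T1), 6 (T0-T2), 3.31 (T1-T2); mean 4.01.
- Plateau after T1: 6, 6, 2; mean 4.67.
- Half of the gain lost by T2: 6, 3, 3; mean 4.

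SE ratios, and type I error of unadjusted two-sided 5% contrasts (40,000 simulated trials per scenario), for k = 1, 2, 3:

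| Shape | T0-T1 SE ratio | T0-T1 type I error | T0-T2 SE ratio | T0-T2 type I error |
|---|---|---|---|---|
| Linear | 1.07, 1.21, 1.34 | 3.6%, 1.9%, 1.1% | 0.91, 0.82, 0.77 | 7.4%, 10.7%, 13.0% |
| Plateau | 0.94, 0.88, 0.85 | 6.3%, 8.5%, 9.7% | 0.94, 0.88, 0.85 | 6.3%, 8.3%, 9.6% |
| Half fade | 0.91, 0.82, 0.77 | 7.5%, 11.0%, 13.3% | 1.05, 1.15, 1.24 | 4.1%, 2.5%, 1.7% |

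For gains still rising to T2, let b be the share of the T2 deviation already present at T1. The T0-T1 standard error turns from too large to too small when b² exceeds the mean of b², 1 and (1 − b)². That is b² + 2b − 2 > 0, or b > √3 − 1 = 0.73.

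**3. Patient intercept with visit-specific residual variances.** The residual variance implied at T1 is half of (T0-T1 + T1-T2 − T0-T2), which under linear divergence is e² − 12s². While this is positive the changes are fitted closely. When e² < 12s² it is held at zero and T0-T2 is understated. For k = 1, 2, 3 under linear divergence the SE ratio is 1.00 throughout for T0-T1, and 1.00, 0.97, 0.88 for T0-T2. Under a plateau both are 0.99. Under the half fade the zero bound falls on T2 instead (implied residual 1 − k²/4 in units of e²), and T0-T1 is 1.00, 0.97, 0.88.

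**4. Unstructured covariance.** Each contrast has its own variance (t on 28 df with complete data). Type I error is 4.8% to 5.2% in every scenario.

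**5. Can both terms be kept?** An unstructured 3 × 3 matrix has 6 parameters. Adding a patient variance makes 7 for 6 moments, which cannot be identified.

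**The case against.** **The article does not commit to a lone random intercept.** It also makes time a repeated measure, and in SPSS a repeated factor can carry its own covariance. The structure is often left to a full protocol or SAP. This stands: constant residual variance is one reading, and silence on the structure is not the fault raised here. But the patient term is stated, and by step 5 it cannot sit beside an unstructured matrix. So the repeated part can be at most a simpler structure unless the stated term is dropped.

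**A fixed direction does not follow.** A reader might infer that the T0-T1 standard error is always too large and the T0-T2 one too small. That needs patients to keep diverging roughly linearly to week 7. Stimulation and the protocol's daily speech therapy both end at 3 weeks, so a plateau or fade is at least as plausible, and either makes T0-T1 too narrow. The documents support no single direction.

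**The error rates are not those of the planned procedure.** This also stands. Section 2.6 tests time points only after a significant interaction and gives Bonferroni as the example. For linear divergence with rate SD 0.5 to 1.5 points per week, error SD 2 to 3 and the constant-residual model, gating and correcting for three comparisons lowers false T0-T2 claims from 8.1-15.3% to 3.0-7.8%. At rate SD 0.5 they fall below 5%. The interaction test itself rejects in 5.4-8.0%. If the post-hoc tests compare arms at each visit rather than changes, SE ratios are only 0.93-1.05 with a between-patient SD of 20.

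**Every SD is assumed.** True. With equal recovery across patients, the stated model is sound.

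**Conclusion.** The point holds conditionally. If section 2.6 means a patient intercept with constant residual variance, unequal recovery makes the T0-T1 and T0-T2 standard errors wrong in either direction. Across the shapes examined they run from 23% too small to 34% too large for T0-T1, and from 23% too small to 24% too large for T0-T2. If residual variances differ by visit, T0-T1 is essentially correct under linear divergence and plateau, and T0-T2 is understated only under strong continuing divergence. The one exception found for T0-T1 is a strong fade, where its standard error is up to 12% too small.

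These sizes rest on assumed SDs, complete data, visits at weeks 0, 3 and 7, and unadjusted 5% contrasts. The documents do not support saying that the trial's error rate will be inflated by a given amount, or that the primary test will lose power. They do support replacing a stated model term with one that is right under every shape examined.

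**What to change.** In 2.6, for WAB-R, replace the patient random effect with an unstructured covariance over T0, T1 and T2, using the repeated part only, with Satterthwaite degrees of freedom. Keep group, visit and group-by-visit as fixed effects, and take the between-arm T0-T1 and T0-T2 change contrasts from that model. Do the same for SAQOL-39 g, which Table 1 schedules at the same three visits. EEG, ERP and blood have two visits in Table 1, so they have only one change and are not affected.

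The cost is one sentence. SPSS can fit the model and no new data are needed. The downside is six covariance parameters instead of two (four with visit-specific residuals). If equal correlation is true, intervals are about 2% wider: the 97.5% t quantile is 2.048 on 28 df against 2.003 on 56, a ratio of 1.02. Simulated power in that case was 78% against 79%.

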#### Sample size

2.2.4

Based on the preliminary experimental results, the effect size [f(V)] for the piTBS group compared to the sham group in the primary outcomes is 0.25. With a significance level (α) of 0.05 and a power (1-β) of 0.95, considering a two-group design involving before and after treatment, and during follow-up assessments conducted at three time points, the anticipated sample size calculated using G*Power 3.1.9.7 for the repeated measures ANOVA model was 28. Anticipating a dropout/exclusion rate of around 10%, a total of 30 patients will need to be enrolled, with 15 patients allocated to each group.

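### The primary outcome is one before-to-after change in WAB-R, but no test of it is named: a T0–T1 conclusion comes only as a post-hoc comparison after a group-by-time interaction

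*Protocol article*

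**What the plan says.** Section 2.6 (Data analysis) defines the outcome: "The primary outcome is the change in WAB-R scores before and after treatment". Section 2.1 labels T0 as before treatment, T1 as after treatment and T2 as the 4-week follow-up, so the declared outcome is the T0–T1 change. Table 1 schedules WAB-R at all three visits.

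The analysis is a linear mixed model with group as a fixed effect, time as the repeated measure and patients as random effects. The rule for reaching a conclusion about particular visits is: "If significant interaction effects between groups and time points are revealed by the LMM, post-hoc comparisons will be conducted to identify the time points". Bonferroni-corrected pairwise comparisons are offered as an example of the method. The number of comparisons is not given, nor whether they compare levels or changes.

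Section 2.2.4 (Sample size) sizes the trial on a repeated measures ANOVA: "considering a two-group design involving before and after treatment, and during follow-up assessments conducted at three time points". Its other inputs are "With a significance level (α) of 0.05 and a power (1-β) of 0.95" and an effect size f(V) of 0.25. The result "for the repeated measures ANOVA model was 28", raised to 30 (15 per arm) for dropout.

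**The concern.** The outcome is one comparison between two arms over one interval. The stated rule does not test it directly. With T0, T1 and T2 in the model, the interaction has 2 degrees of freedom and responds to any difference in profile, including one that arises only after T1. The pre-declared comparison is then treated as post hoc, available only if that test is significant and possibly judged at 0.025 or 0.0167. A single pre-named contrast has no multiplicity to correct.

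Two consequences follow, depending on which step is decisive. If it is the post-hoc comparison, a true T0–T1 effect can be missed at the gate or at the corrected threshold. If it is the interaction, the trial can be called positive with nothing happening between T0 and T1. These belong to alternative readings and should not be added together.

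**Working it through.** **The plan's own figure.** For the group-by-time interaction, λ = f²·N·m/(1−ρ), with 2 and 2(N−2) degrees of freedom, m = 3 visits and f = 0.25 read as an ordinary Cohen f. The correlation ρ between visits is not stated.
- ρ = 0.5, N = 28: λ = 0.0625×28×3/0.5 = 10.5; critical F(2, 52) = 3.175; power 81%.
- ρ = 0.5, N = 30: λ = 11.25; power 84%. Reaching 95% would need N = 44.
- ρ = 0.7, N = 28: λ = 17.5; power 96%.

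So 28 patients give the planned 95% only at an unstated correlation of about 0.70. That is a separate matter, but it shows why two starting points are used below.

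**Effect sizes.** If the between-arm effect is e at T1 and either nil or fully sustained at T2, then f = e/√18. So f = 0.25 gives e = 0.25×4.243 = 1.061 outcome SDs. The SD of a change is √(2(1−ρ)), which is 1 at ρ = 0.5 and 0.775 at ρ = 0.7. In SDs of change, the effect is therefore 1.061 at ρ = 0.5 and 1.369 at ρ = 0.7.

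**Direct T0–T1 test.** This is a two-sample t-test on change with 15 per arm, 28 df and noncentrality δ√(15/2).
- δ = 1.06: noncentrality 2.90, power 80%.
- δ = 1.364: noncentrality 3.74, power 95%.

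The 80% and 95% starts thus correspond closely to the plan's f = 0.25 at assumed correlations of 0.5 and 0.7, for those two T2 patterns.

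**Gate and Bonferroni.** The event simulated is interaction p < 0.05 and T0–T1 contrast p < 0.05/k. Assumptions: 15 per arm, complete data, compound symmetry, and at least 20,000 trials per scenario. The T1 effect is held at the 80% or 95% size, and the T2 effect is a fraction of it.

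| T2 effect / T1 effect | 80% start: gate only | k = 2 | k = 3 | 95% start: gate only | k = 2 | k = 3 |
|---|---|---|---|---|---|---|
| 0 | 76% | 69% | 63–64% | 94% | 91% | 88% |
| 0.5 | 70% | 67% | 63% | 91% | 89% | 87% |
| 0.75 | 72% | 67% | 63% | 92% | 89% | 87% |
| 1 | 76% | 69% | 63–64% | 94% | 90% | 87% |

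Using the model's pooled error instead of separate t-tests, with the 80% effect size and T2 nil or sustained, gives 71% (k = 2) and 67% (k = 3), against 81% for the direct test.

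**Source of the loss.** Bonferroni with no gate takes 80% to 70% (k = 2) or 64% (k = 3). The gate alone takes it to 70–76%. Bonferroni usually costs more. The exceptions are partial T2 effects with two comparisons, where the gate does most of the damage.

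**Interaction as the decision.** Put the 80% effect (δ = 1.06) at T2 only. Then λ = 7.5×(2/3)×2×1.06² = 11.24 on 2 and 56 df, and the interaction is significant 84% of the time with no T0–T1 difference.

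**The case against.** The strongest reply is that the interaction is the main test. Section 2.2.4 sizes a three-visit repeated measures analysis, and the post-hoc step only locates the difference. On that reading no Bonferroni penalty touches the main test. This is coherent, but it leaves the decisive test answering a different question from the declared outcome.

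Conversely, if the post-hoc step decides, a T2-only effect would be located at T2, and T1 would be falsely credited rarely (about 1.7% of the time with three corrected comparisons). The 84% figure is therefore no harm on that reading.

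Three further points stand:
- Bonferroni is an example and the number of comparisons is open, so 0.0167 is an assumption.
- Section 2.6 does not say which visits enter the WAB-R model. The same post-hoc rule is repeated for EEG and ERP, which Table 1 schedules only at T0 and T1. If WAB-R were modelled on T0 and T1 alone, the interaction would be exactly the contrast wanted. The sample size wording ("during follow-up assessments conducted at three time points") and Table 1 point to three visits but do not settle it.
- Detailed contrast specification is usual analysis-plan content. The point here is narrower: the article does state a decision rule, and that rule does not match its stated outcome.

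A reader might infer that planned power drops from 80% to 63–69%. The document gives no 80%; it states 0.95. A reader might also infer an inflated type I error for the T0–T1 claim. A gate followed by Bonferroni is conservative, so that does not follow.

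**Conclusion.** The mismatch is real and is in the current text: one before-to-after outcome, no named test of it, and a T0–T1 conclusion available only after an interaction test. Its cost depends on the reading.

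- **Post-hoc comparison decisive.** A direct test at the planned 95% falls to about 87–91%, so the chance of missing a true effect rises from 5% to roughly 9–13%. From an assumed 80%, power falls to about 63–69%.
- **Interaction decisive.** There is no such penalty, but the test can be significant on T2 alone, about 84% of the time for the 80% effect size.

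These sizes are illustrations. They rest on the assumed correlation structure, complete data, contrasts of change, two or three comparisons and the assumed course of the effect to T2, none of which the protocol fixes.

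**What to change.** In section 2.6, state that the primary test is the between-arm difference in WAB-R change from T0 to T1, estimated as one contrast from the mixed model, at two-sided 0.05, made whatever the result of the interaction and without multiplicity correction. Then state that the interaction and the contrasts involving T2 are secondary.

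This costs two sentences and no patients, visits or data. The small downside is that T2 data no longer count directly towards the primary test. At the 80% effect size, fully sustained to T2, the interaction alone would be significant 84% of the time against 80% for the contrast, but it would not establish an effect at T1.
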